## Abstract

**Background:**

Leg cramps are painful sensations of tightening in the muscles of the legs that commonly appear during the night and are often associated with secondary insomnia. They are common especially in older age. There is no evidence that any method of prevention of nocturnal leg cramps is both safe and effective. There are no previous trials concerning cramp prevention by using compression stockings. The objective of this study is to assess in a prospective randomised controlled trial whether leg cramps can be prevented by the daily use of knee-length compression stockings or magnesium supplements.

**Methods:**

The study will be set in Finland, and 50–84-year-old volunteers will be recruited through Google Ads, the Finnish health library website and Finnish primary health care centres. The participants must have a minimum of two episodes of leg cramps per week for the past 4 weeks to be included in the study. The participants (*n* = 225) will be allocated to three equal groups: the compression stocking arm, the magnesium supplement arm and the placebo arm. The participants will go through 4 weeks of follow-up without intervention and then another 4 weeks of follow-up with the assigned intervention. The material for the study will be collected through electronic questionnaires.

**Discussion:**

This protocol describes a study that compares compression stockings, magnesium supplements and placebo for the prevention of leg cramps. The results of this study can significantly improve knowledge on the methods of preventing leg cramps.

**Trial registration:**

ClinicalTrials.gov NCT04694417. Registered on Jan 4, 2021.

## Administrative information

Note: the numbers in curly brackets in this protocol refer to SPIRIT checklist item numbers. The order of the items has been modified to group similar items (see http://www.equator-network.org/reporting-guidelines/spirit-2013-statement-defining-standard-protocol-items-for-clinical-trials/).

## Introduction

### Background and rationale {6a}

Leg cramps are sudden, painful episodes of involuntary tightening sensations that appear usually in the calf, thigh or foot muscles. The cramp lasts for an average of 9 min and can be relieved by powerful stretching of the affected muscle [1]. The symptom appears commonly during the night [1–3] and is often associated with secondary insomnia [1]. Some 30–50% of elderly outpatient clinic patients suffer from leg cramps, and less than half of them seek medical help because of these cramps [2, 3]. The incidence increases with age [3].

The exact aetiology is unclear. High-intensity exercises, nerve dysfunction and metabolic causes have been associated with nocturnal leg cramps [1]. Several medications and medical conditions have also been associated with muscle cramps [4]. Most cases are idiopathic [1].

Safe and effective treatments for nocturnal leg cramps have not been found [1]. Passive stretching, massage and mild exercises before going to bed are often used, but the evidence for their effectiveness is limited [1, 5]. Quinine has a modest effect on nocturnal leg cramps, but it is no longer in use because of drug interactions and serious adverse effects [6, 7]. The evidence for using magnesium to prevent nocturnal leg cramps has been contradictory [8, 9]. In a recently updated Cochrane systematic review, it was concluded that it is unlikely that magnesium supplementation provides cramp prophylaxis for older adults. However, there are no high-quality studies concerning exercise-associated muscle cramps or disease-state-associated muscle cramps [10]. Many other medications have also been suggested, such as carisoprodol, diltiazem, gabapentin, orphenadrine, verapamil and vitamin B_12_, but the evidence for their effectiveness is limited [1].

An article concerning cramps in the Finnish health library website for the general public [11] has yielded around 25 feedbacks from the readers, most of which highlight experience that using knee-length compression stockings could help to prevent nocturnal leg cramps. Compression stockings are not a standard of care currently, and there are no previous trials investigating the effectiveness of compression stockings for leg cramp prevention. There are no evidence-based guidelines on the treatment of leg cramps, but magnesium supplements are commonly used for this purpose. The main aim of this study is to assess the efficacy of knee-length compression stockings compared to magnesium supplements in a randomised controlled trial.

### Objectives {7}

The main outcomes are as follows:
The frequency of manifestation of the cramps.The intensity of the cramps.The quantity of nocturnal awakening because of the cramps.

### Trial design {8}

The study will be carried out as a randomised controlled trial. The participants will be randomised into three parallel treatment arms: compression stocking group, magnesium supplement group and placebo group. The groups will be of equal size. The participants will be blinded in the tablet arms. The framework is a superiority study between the three arms.

The participants will be recruited online via advertisements on Google and the national health library’s article on cramps. The outcomes of the study will be obtained using consecutive electronic questionnaires. The main outcome measures will be based on the participants’ record-keeping (collection of data on both symptoms and intervention adherence).

## Methods: participants, interventions and outcomes

### Study setting {9}

The study will be set in Finland and include voluntary participants, who will be recruited and followed online.

### Eligibility criteria {10}

Baseline information will be collected with an electronic questionnaire e-mailed to self-identified possible study subjects who have filled out an electronic contact information form. Based on the questionnaire, the researchers will decide whether the participants are suitable to participate in the study and the unsuitable individuals will be excluded at this stage. The subjects must have a functioning Internet connection and e-mail in active use to be able to participate.

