#### Exclusion criteria

Peripheral artery disease (confirmed or suspected).Peripheral artery bypass surgery.Grave peripheral neuropathy or any sensory disorder.Allergy to the material of the compression stockings.Grave renal failure (GFR under 30 ml/min).The use of a magnesium carbonate product (e.g. Rennie® or Berocca®).Cardiac failure with pulmonary oedema or massive lower limb swelling.Lower limb soft tissue problems, including skin transplant, thinned skin, varicose ulcer, necrosis and any infection.Lower limb deformity or atypical shape or size that could prevent the usage of compression stockings.Continuous usage of compression stockings for any other reason than leg cramps.

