### Intervention description {11a}

#### Compression stockings

Compression stockings are mainly used for the prevention and reduction of lower limb oedema or venous thrombosis. There are three compression classes used in health care [12]. The compression stocking arm of the study will receive CE-marked stockings within the compression class 1 (20 mmHg or less compression). The correct size for the compression stockings will be defined by the reported circumference of the participant’s ankle and calf. If a participant measures the size incorrectly, a new pair of compression stockings will be sent to them in a different size based on their feedback. The participants will be given instructions to put the stockings on immediately after getting out of bed in the morning and to take them off before going to bed in the evening for the last 4 weeks of the study. Stockings within the mild compression class have no harmful effects on individuals when the exclusion criteria are considered and the size is configured appropriately [12]. The participants will be instructed to communicate with a dedicated research assistant via e-mail or phone in case of any problems or questions.

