#### Magnesium

Magnesium is a mineral substance which regulates many biochemical reactions in the body, for example protein synthesis and the function of the muscles and nerves. It has a significant role in controlling blood sugar, blood pressure, energy generation and the formation of the bones. The recommended dietary allowance for magnesium is 420 mg for males and 320 mg for females over 50 years old. Dark green vegetables, leguminous plants, nuts, seeds and whole grains are good sources of magnesium [13, 14].

In the average Finnish diet, the recommendation is usually exceeded, and excessive amounts of magnesium in the body are extremely rare [15]. The magnesium arm of the study will take oral tablets containing 630 mg of magnesium hydroxide daily for the last 4 weeks of the study, which is equivalent to 250 mg of pure magnesium per day. The magnesium tablets for this study were manufactured and analysed by the Pharmia pharmaceutical company in Finland.

Magnesium does not accumulate excessively in the body through diet or oral supplements except in situations of renal failure, metabolic acidosis or advanced old age. Magnesium hydroxide tablets should not have any harmful effects on individuals when the excluding criteria are considered. The most common side effect of oral magnesium hydroxide is osmotic diarrhoea (1–2% of patients) or other irritation of the gastrointestinal tract [13, 14].

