### Criteria for discontinuing or modifying allocated interventions {11b}

The allocated intervention can be discontinued at any stage of the study in response to harm or the participant’s request. Possible harms are, for example, an allergy to the material of compression stockings, allergy to an ingredient of either magnesium or placebo tablets, magnesium-induced diarrhoea or inability to find suitable compression stockings. Participants can drop out of the study at any time for any reason without consequences. Any harms reported to the research assistant will be recorded. Allocated interventions cannot be modified.

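### The exclusions are checked once, by self-report, at least 28 days before first product use, and no described route asks about them again, although the stated safety of the products depends on them

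*Protocol article*

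**What the plan says.** **One check, at entry.** Eligibility criteria {10} describes a single decision based on the e-mailed baseline questionnaire: "the unsuitable individuals will be excluded at this stage". Included people are then told when to start observing their cramps ({26a}). Sequence generation {16a} places allocation after the baseline evaluation. Neither the allocation sections nor the description of posting the products mentions a second check.

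**Timing.** The Abstract and {18a} give 4 weeks without treatment, then 4 weeks with the assigned product.

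**Follow-up content.** {18a} describes weekly reporting of cramp frequency, intensity and night waking, with the same form used in both periods. Trial design {8} adds adherence. {18a} closes by saying that other symptoms, health and lifestyle changes will not be monitored.

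**Exclusions that can change.** The ten exclusions include confirmed or suspected peripheral artery disease and these three:
- "Lower limb soft tissue problems, including skin transplant, thinned skin, varicose ulcer, necrosis and any infection"
- "Cardiac failure with pulmonary oedema or massive lower limb swelling"
- the renal criterion, which begins "Grave renal failure (GFR under 30 ml/min"

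**Safety statements tied to the exclusions.** For stockings: "Stockings within the mild compression class have no harmful effects on individuals when the exclusion criteria are considered and the size is configured appropriately". For magnesium: "Magnesium hydroxide tablets should not have any harmful effects on individuals when the excluding criteria are considered". The magnesium section also says that the mineral does not build up excessively "except in situations of renal failure, metabolic acidosis or advanced old age". The Strengths section makes a similar conditional statement for the interventions in general.

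**Existing routes.** Participants get a weekly e-mail, and missing forms are chased by e-mail and then phone ({11c}, {18b}). They can contact the research assistant with any problem. A product may be stopped at any stage because of harm or on request, and {11b} adds: "Any harms reported to the research assistant will be recorded". Reported harms are discussed at once in the research group ({22}).

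**The concern.** The protocol argues that the products are safe provided the exclusions are respected. That condition matters while the product is in use, but it is tested only before the untreated run-in. Participants are 50 to 84 years old, and a leg infection, an ulcer, or new heart failure with leg swelling can arise within eight weeks. The Strengths section notes that participation needs no appointments, so the trial itself gives no clinician an occasion to notice such a change.

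The routes that exist respond to unreturned forms, or to problems and harms that the participant reports. A participant with a new leg infection may not see it as a study matter, and nothing in the described weekly form prompts them to mention it.

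What is at stake is the safety of a small number of people, mainly in the stocking arm, because three of the four conditions bear chiefly on compression. The renal criterion bears on the magnesium arm. The primary comparison is not threatened.

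**Working it through.** **The plan's own figure.** The point does not depend on the sample size, which is used here only for the arm size. For a one-way analysis of variance with three groups, f = 0.25, two-sided 0.05 and 80% power, the minimum total is 158 (power 0.802). Allowing for 30% drop-out, 158 / 0.70 = 225.7, or 226, against 225 stated. It reproduces to within one person. Per arm: 225 / 3 = 75.

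**Age of the only check** (4 + 4 weeks, from the Abstract and {18a}):
- at first use: 4 × 7 = 28 days
- at the end of use: 8 × 7 = 56 days

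Both are minimum values, because the wait between the eligibility decision and the start date comes on top.

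**Which exclusions can newly arise.** Of the ten listed, at least four can appear or worsen within 8 weeks: a soft tissue problem of the leg, cardiac failure or massive swelling, peripheral artery disease, and severe renal failure. This count is a judgement, not a calculation.

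**Illustrative size.** The documents give no incidence. Assume, for illustration only, that any new exclusion condition arises at a rate r of 1% to 10% per year. The expected number among m people over w weeks is m × (1 − exp(−r × w / 52)).

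| People | By first use (w = 4) | By end of use (w = 8) |
|---|---|---|
| Stocking arm, m = 75 | 0.06 to 0.57 | 0.12 to 1.15 |
| All arms, m = 225 | 0.17 to 1.72 | 0.35 to 3.44 |

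The stocking row is the more relevant one, because the lower row includes the placebo arm. On this assumed range, about one person in the stocking arm at most would be affected.

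**With a prompt from week 3.** The week-3 form is completed at day 21, so the answer is 28 − 21 = 7 days old at first use, and it is renewed every 7 days. Burden: 1 item × 6 forms (weeks 3 to 8) = 6 answers per participant.

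**The case against.** The strongest reply is that much of this rests on silence in a condensed article. A statement of when unsuitable people are excluded does not say that nobody is stopped later. The sentence on not monitoring health stands under outcome collection and may describe only trial data. Safety has its own sections. The instructions posted with the product and the participant information are not shown, and either could tell people when not to use a product. Contact is active, and a product can be stopped at any stage. Finally, a questionnaire item is still self-report: it cannot detect a silent fall in GFR or artery disease that no clinician has yet suspected.

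Most of this stands as a limit on size. A reader might infer that a new condition would come to light only if the participant volunteered it, or that the trial has no safety follow-up. The documents do not support either reading, given the weekly contact, the chasing of missing forms, the recording and discussion of harms, and the material not shown.

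The reply does not remove the point. The article states that health will not be monitored, describes a weekly form limited to cramps and adherence, and makes product safety conditional on criteria that no described route asks about again. That is a stated arrangement with a small avoidable cost, not mere silence.

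**Conclusion.** The point holds as a minor participant-safety weakness. The only described check of the exclusions is by self-report, at least 28 days old at first use and at least 56 days old at the end of use. The concern lies mainly with leg and cardiac conditions in the stocking arm, about 75 people wearing class 1 stockings for 4 weeks. The renal item in the magnesium arm is a lesser part, because a self-report prompt can pick up only what a clinician has already diagnosed.

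Few cases are expected. The illustrative numbers rest wholly on an assumed incidence, and no case count is claimed. The conclusion also assumes that the unshown instructions and participant information do not already ask for new exclusion conditions to be reported; if they do, the gap is smaller still. It would be wrong to infer that the safety statements are false, or that power, sample size or the primary analysis is affected. No analysis figure changes.

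**What to change.** **Weekly item.** Add one yes/no item, identical in all arms, to the existing form from week 3 to week 8. It asks about any new condition among these:
- leg infection, ulcer or another listed soft tissue problem
- heart failure or massive leg swelling
- confirmed or suspected peripheral artery disease
- severe renal failure diagnosed by a clinician

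Starting at week 3 leaves the last run-in week for following up a positive reply, so the two 4-week periods keep their dates.

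**Action on a yes.** The participant is contacted. If the condition is confirmed, the product is withheld or stopped under {11b}. Magnesium and placebo follow the same rule, so that stopping does not reveal which tablet was taken.

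**Text changes.** Amend the closing sentence of {18a} to allow this check. Amend {18b}, which now collects weekly questionnaires only until discontinuation, so that cramp data continue after a product is stopped. Everyone is analysed as randomised, as the intention-to-treat statement in {20a} already requires.

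**Cost.** One extra item on six existing forms, brief follow-up of positive replies, and two amended sentences. A few people whose product is withheld or stopped would still count in their arm, which could slightly dilute the stocking effect.

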#### Inclusion criteria

Minimum of 2 leg cramps per week in the past 4 weeks.Age from 50 to 84 years.

A minimum of 2 leg cramps per week is thought to be sufficient for the response to treatment to be seen with this trial setting. Higher demand of symptoms could significantly complicate study recruitment. The age range of 50–84 is derived based on the perception that in younger people the aetiology of cramps is often different.

#### Exclusion criteria

Peripheral artery disease (confirmed or suspected).Peripheral artery bypass surgery.Grave peripheral neuropathy or any sensory disorder.Allergy to the material of the compression stockings.Grave renal failure (GFR under 30 ml/min).The use of a magnesium carbonate product (e.g. Rennie® or Berocca®).Cardiac failure with pulmonary oedema or massive lower limb swelling.Lower limb soft tissue problems, including skin transplant, thinned skin, varicose ulcer, necrosis and any infection.Lower limb deformity or atypical shape or size that could prevent the usage of compression stockings.Continuous usage of compression stockings for any other reason than leg cramps.

### Who will take informed consent? {26a}

Participants included based on the criteria mentioned above will receive an e-mail, which contains information about the study protocol and the date when they are supposed to start observing their leg cramps daily. A consent form will be sent by post, along with a request to sign and return it to the principal investigator. Excluded individuals will also be informed by e-mail.

### Additional consent provisions for the collection and use of participant data and biological specimens {26b}

Not applicable.

### Pilot study

A pilot study was carried out from March 23 to August 9, 2020, with 12 participants. It showed that recruitment was slower than expected, this being the most important challenge of the protocol. Communication with the participants was fluent and engagement in the trial was very good—only one of the participants dropped out of the study. No significant side effects were observed. Minor amendments were made in the questionnaires after the pilot study based on feedback from the participants. Of the 12 participants, 11 would recommend participating in the study to a friend.

## Interventions

### Explanation for the choice of comparators {6b}

The comparators were chosen based on the popularity of magnesium supplements that are extensively marketed for cramp prevention, patient-reported experiences of compression stockings described above, and previous evidence (or lack of evidence). The placebo arm will act as a control group for the magnesium arm.

### Intervention description {11a}

#### Compression stockings

Compression stockings are mainly used for the prevention and reduction of lower limb oedema or venous thrombosis. There are three compression classes used in health care [12]. The compression stocking arm of the study will receive CE-marked stockings within the compression class 1 (20 mmHg or less compression). The correct size for the compression stockings will be defined by the reported circumference of the participant’s ankle and calf. If a participant measures the size incorrectly, a new pair of compression stockings will be sent to them in a different size based on their feedback. The participants will be given instructions to put the stockings on immediately after getting out of bed in the morning and to take them off before going to bed in the evening for the last 4 weeks of the study. Stockings within the mild compression class have no harmful effects on individuals when the exclusion criteria are considered and the size is configured appropriately [12]. The participants will be instructed to communicate with a dedicated research assistant via e-mail or phone in case of any problems or questions.

#### Magnesium

Magnesium is a mineral substance which regulates many biochemical reactions in the body, for example protein synthesis and the function of the muscles and nerves. It has a significant role in controlling blood sugar, blood pressure, energy generation and the formation of the bones. The recommended dietary allowance for magnesium is 420 mg for males and 320 mg for females over 50 years old. Dark green vegetables, leguminous plants, nuts, seeds and whole grains are good sources of magnesium [13, 14].

In the average Finnish diet, the recommendation is usually exceeded, and excessive amounts of magnesium in the body are extremely rare [15]. The magnesium arm of the study will take oral tablets containing 630 mg of magnesium hydroxide daily for the last 4 weeks of the study, which is equivalent to 250 mg of pure magnesium per day. The magnesium tablets for this study were manufactured and analysed by the Pharmia pharmaceutical company in Finland.

Magnesium does not accumulate excessively in the body through diet or oral supplements except in situations of renal failure, metabolic acidosis or advanced old age. Magnesium hydroxide tablets should not have any harmful effects on individuals when the excluding criteria are considered. The most common side effect of oral magnesium hydroxide is osmotic diarrhoea (1–2% of patients) or other irritation of the gastrointestinal tract [13, 14].

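### The statement that magnesium tablets should be harmless leans on the exclusion criteria, but no criterion covers metabolic acidosis, and tablet-ingredient allergy is not excluded either

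*Protocol article*

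**What the plan says.** The Magnesium part of Intervention description {11a} states that magnesium from diet or oral supplements does not accumulate excessively "except in situations of renal failure, metabolic acidosis or advanced old age". The sentence that follows draws the safety conclusion: "Magnesium hydroxide tablets should not have any harmful effects on individuals when the excluding criteria are considered".

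Two entries in the eligibility lists bear on those three states. The Exclusion criteria name "Grave renal failure (GFR under 30 ml/min"), and the Inclusion criteria require "Age from 50 to 84 years".

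On allergy, the Exclusion criteria list "Allergy to the material of the compression stockings". The section Criteria for discontinuing or modifying allocated interventions {11b} gives examples of possible harms. They include allergy to the stocking material and "allergy to an ingredient of either magnesium or placebo tablets".

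On how entry is decided, Eligibility criteria {10} says that, from an electronic baseline questionnaire, "the researchers will decide whether the participants are suitable to participate in the study". The consent section {26a} then says: "Participants included based on the criteria mentioned above will receive an e-mail".

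**The concern.** The protocol names three states in which magnesium may accumulate and, in the next sentence, makes the exclusion criteria the ground for expecting no harm. A reader would expect the list to deal with each of the three. For metabolic acidosis it does not.

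The list carries real weight in this trial. Applicants identify themselves online, eligibility is judged from a questionnaire, no samples are collected, and participation needs no appointment. The Strengths section repeats that the interventions have no serious effects in general provided the exclusion criteria are complied with. Section {18a} says that other symptoms and the participant's health will not be monitored during follow-up, so a problem would come to light mainly if the participant reported it.

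One entry list also has to clear each applicant for all three arms, because nobody knows the allocation at consent. The list screens for stocking allergy but not for tablet-ingredient allergy, although two of the three arms take tablets. At stake is the safety of a very small number of people and the soundness of the printed safety rationale. The comparison between arms is not affected.

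**Working it through.** No figure in the protocol bears on this point, so there is nothing to reproduce. The check sets the named risks beside the printed criteria.

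**Step 1: the three accumulation states against the lists.** All ten exclusion criteria and both inclusion criteria were read.

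| State named under Magnesium | Matching criterion | Coverage |
|---|---|---|
| Renal failure | Exclusion: GFR under 30 ml/min | Partial: severe failure only |
| Advanced old age | Inclusion: upper age limit 84 | Partial: people up to 84 remain eligible, and the age range is justified by aetiology in younger people, not by accumulation |
| Metabolic acidosis | None | None stated |

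The other exclusions concern peripheral arteries (disease, bypass surgery), neuropathy or sensory disorder, stocking-material allergy, magnesium carbonate products, cardiac failure, lower-limb soft tissue, limb shape, and existing stocking use. None of them names acidosis. The GFR limit may remove some people whose acidosis is of renal origin, but the document does not say so, and acidosis from other causes would remain.

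**Step 2: allergy.**

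| Possible harm named in {11b} | Exclusion criterion |
|---|---|
| Allergy to stocking material | Yes |
| Allergy to an ingredient of either tablet | None |

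The placebo ingredients are printed (microcrystalline cellulose, magnesium stearate, silicon dioxide). For the magnesium tablet only magnesium hydroxide is named.

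**Step 3: chance of allocation to the relevant tablet.** Allocation is 1:1:1.

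- Magnesium: 1/3, or 225 / 3 = 75 of the planned participants.
- Either tablet: 2/3, or 2 × 75 = 150.
- An enrolled person with metabolic acidosis would have a 1 in 3 chance of receiving magnesium.
- An enrolled person allergic to an ingredient would have a 1 in 3 chance of receiving it if it is in one tablet only, and 2 in 3 if it is in both.

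**Step 4: expected number of people.** This would need the prevalence of each condition among applicants and the share that the suitability check lets through. The document gives neither, so no count is offered.

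**The case against.** The strongest reply is that enrolment of a known case is not shown. The suitability decision sits inside the eligibility section, so the criteria that the consent section refers back to can be read as including it. If the questionnaire already asks about acidosis or allergies, the gap is one of wording only. This stands as a limit on the point: a reader might infer that applicants with metabolic acidosis will be enrolled, and the document does not support that. It does not remove the mismatch, because the safety sentence appeals to the excluding criteria, and a discretionary judgement on an unseen form is not one of them. Nor is this a matter of detail left to a fuller protocol: the article prints both the list and the assurance built on it.

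Second, the assurance is hedged and the setting is mild. It says what should be the case, the next sentence names diarrhoea and gastrointestinal irritation, excess body magnesium is described as extremely rare, and the dose is 250 mg of magnesium a day for 4 weeks. This stands and supports a low rating.

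Third, other safeguards exist. Applicants are told of possible downsides before consenting and can decline. Four untreated weeks with weekly contact come before any tablet is taken. After that, the intervention can be stopped, harms reported to the research assistant are recorded and discussed, and unblinding is available. This stands too. However, the early steps depend on the applicant seeing the relevance of the condition, and stopping, recording and unblinding follow exposure.

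Fourth, the list of harms in {11b} gives examples of reasons to stop, and not every harm there needs a matching exclusion; diarrhoea is among them. That is fair, and it is why the allergy gap is secondary. Yet a known allergy can be asked about beforehand, the list already does so for the stockings, and a tablet allergy is no harder to ask about. A first reaction cannot be screened out.

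**Conclusion.** The point holds as a mismatch between printed statements. Metabolic acidosis is named as a state in which magnesium may accumulate, the no-harm statement rests on the exclusion criteria, and no criterion covers it. Tablet-ingredient allergy is a second, smaller gap of the same kind.

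The point is minor: a change worth making, not one the trial depends on. The absolute risk is probably very small, cannot be quantified from the document, and alters no estimate, test or sample size.

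Two stronger readings should be resisted. One is that the tablets are unsafe for the population as recruited; nothing in the document shows that. The other is that one added criterion would make the safety sentence correct as it stands. It would not. A self-reported exclusion catches only known acidosis and no samples are taken, renal failure is excluded only at GFR under 30, and people up to 84 stay eligible. The sentence itself therefore needs narrowing.

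The conclusion assumes that the printed eligibility lists are complete. It makes no assumption about what the questionnaire asks.

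**What to change.** Make three changes.

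1. Add two lines to the Exclusion criteria: *Known metabolic acidosis*, and *Known allergy to an ingredient of the magnesium or placebo tablets*.
2. Ask about both as known history in the baseline questionnaire. If it already asks, only the list needs changing.
3. Narrow the safety sentence under Magnesium. It should say that known cases of the named conditions are excluded, with renal failure excluded only at GFR under 30 and age only above 84.

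The cost is a small eligibility amendment and two questionnaire items after enrolment has started (May 2021, Trial status). If it is treated as a major modification, section {25} already sets the route: discussion in the research group and with the ethics committee, and information to participants. No test, record check or appointment is added, and very few applicants should be lost. As an entry criterion, the change helps only those who apply after it.
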